#### Secondary endpoints

2. En bloc resection rate

En bloc resection is defined as the complete removal of the lesion in a single piece without residual visible tumors.3. Procedure time

Procedure time refers to the duration from submucosal injection to completion of the resection. It does not include the time required for prophylactic clipping, covering methods, or endoscopic coagulation of visible vessels after resection.4. Adverse events (AEs)Adverse events will be monitored and recorded, including the following:a. Delayed bleeding: bleeding that occurs within 28 days after colonoscopy withdrawal that requires hemostasis.b. Intraoperative perforation: defect in the muscular layer observed during the procedure, or the presence of free air in the peritoneal cavity on imaging studies performed within 12 h after treatment.c. Delayed perforation: bowel perforation within 28 days after the procedure without intraoperative perforation, confirmed by the presence of free air in the peritoneal cavity on imaging studies performed > 12 h after treatment.d. Electrocoagulation syndrome: localized abdominal tenderness and fever (≥ 37.6℃), or inflammatory response without definite evidence of perforation.5. Number of hospitalization days

Outpatient treatment will be considered as 0 days.6. Total cost of the devices and agents

The costs associated with the ESD knife, band ligator device, injection needle, distal attachment, snare, traction device, clips, solution for submucosal injection, and antibiotics are calculated.7. Rate of AEs among groups with and without closure of the resection site

Patients who undergo closure of the resection site using clips or detachable snares will be compared with those without closure.8. Outcomes between expert and non-expert endoscopists

The outcomes of expert endoscopists, defined as those with experience in > 40 colorectal ESD procedures [38, 41]. will be compared with those of non-expert endoscopists.9. Factors associated with failure of R0 resection

The potential factors contributing to the failure of achieving R0 resection, including treatment method, tumor location, tumor size, previous biopsy, and endoscopist expertise, will be analyzed.

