### Eligibility criteria

#### Inclusion criteria

Patients should meet all of the following criteria.1) Patients with a lesion endoscopically diagnosed as rectal NET ≤ 10 mm.2) Patients who are at least 20 years old at the time of obtaining consent.3) Written informed consent should be provided based on the free will of patients after they have thoroughly understood the instructions provided regarding study participation.

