### Serious adverse events

The following AEs are classified as serious: AEs resulting in death or posing a life-threatening risk, AEs requiring rehospitalization for treatment or extension of the hospitalization period, AEs leading to persistent or marked disability, and AEs with the potential to cause birth defects in the offspring. AEs will be assessed and graded according to the Common Terminology Criteria for Adverse Events Version 5.0. If a serious AE occurs, the investigators should report it immediately to the principal investigator. If the principal investigator determines a causal relationship between a serious AE and the protocol treatment, a serious AE report will be submitted to the CRB and the hospital director. In addition, information regarding the occurrence of serious AEs will be shared promptly with all the investigators.

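### Delayed perforation is classified only by intraperitoneal free air on imaging, so in a rectal trial some proven delayed perforations fit none of the listed perforation categories

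*Protocol article*

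**What the plan says.** All references are to the protocol article. Secondary endpoints, item 4, lists four adverse events, a to d. Three matter here.

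- **4c, event and window:** "Delayed perforation: bowel perforation within 28 days after the procedure without intraoperative perforation".
- **4c, confirmation:** "confirmed by the presence of free air in the peritoneal cavity on imaging studies performed > 12 h after treatment". No alternative follows.
- **4b, intraoperative perforation:** "defect in the muscular layer observed during the procedure, or the presence of free air in the peritoneal cavity", the imaging being within 12 h of treatment. Either limb is enough.
- **4d, electrocoagulation syndrome:** ends with "inflammatory response without definite evidence of perforation".

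The list opens with "Adverse events will be monitored and recorded, including the following", so it is not closed. The section on serious adverse events adds that "AEs will be assessed and graded according to the Common Terminology Criteria for Adverse Events Version 5.0".

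Inclusion criteria admit "Patients with a lesion endoscopically diagnosed as rectal NET ≤ 10 mm". Neither the inclusion nor the exclusion criteria limit where in the rectum the lesion may lie.

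**The concern.** Item 4c makes free air inside the peritoneal cavity a necessary condition for calling an event a delayed perforation. That suits an organ lying wholly within the cavity. The rectum does not: its lower part is outside it. This is general anatomy and is not stated in the article. Air from a perforation there may stay outside the cavity, and the definition would then not be met. Nor does it provide for a defect that someone sees directly at repeat endoscopy or at surgery, although 4b accepts exactly that kind of evidence during the procedure.

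At stake is the reported number of delayed perforations, a serious complication for which readers will look at the count in each arm. The Discussion relies on adverse events, with procedure time, hospital days and cost, to assess the simplicity of ESMR-L. With 32 institutions, there is also a risk that some sites follow the literal wording while others label an uncovered case by clinical judgement.

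**Working it through.** This is a check of wording; there is no stated figure to reproduce. I took the ways in which a perforation could come to light and tested each against the three items.

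| Case | 4b | 4c | 4d |
|---|---|---|---|
| 1. Intraperitoneal free air on imaging after 12 h, no intraoperative perforation | No | **Yes** | No |
| 2. Only extraperitoneal air on imaging after 12 h, perforation established | No: air not in the cavity, and too late | No: air not in the cavity | No: perforation is established |
| 3. Defect seen at later endoscopy or surgery, no imaging showing intraperitoneal air | No: not seen during the procedure | No: required imaging finding absent | No: perforation is established |
| 4. As case 3, but imaging after 12 h also shows intraperitoneal air | No | **Yes** | No |
| 5. Only extraperitoneal air on imaging within 12 h, no defect seen during the procedure | No: air not in the cavity | No: air not in the cavity, and too early | No, if perforation is established |

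Cases 2 and 3 are the gap: a proven delayed perforation that meets none of the definitions. Case 4 shows its limit: direct sight is a problem only when imaging does not also show intraperitoneal air. Case 5 shows that the imaging limb of 4b has the same restriction, partly offset there because the operator is looking at the site. The 4d column takes its closing qualifier to govern the whole item. If it governed only the last limb, a febrile, tender patient with a proven perforation could be labelled electrocoagulation syndrome, which is no better.

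No other section widens 4c.

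**Where the count is used.** Statistical analyses specifies Fisher's exact test of adverse event rates by closure of the resection site, and a subgroup analysis of the adverse event rate by endoscopist expertise. It names no test of delayed perforation between ESD and ESMR-L.

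**Size.** Two inputs would be needed: the true rate of delayed perforation and the share of lesions outside the peritoneal cavity. The article gives neither. Purely as an illustration, assume a rate of 0.5 to 1% in the planned 266 patients and a share of 30 to 80%:

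- events: 266 × 0.005 = 1.3 to 266 × 0.01 = 2.7;
- of these, at most 1.33 × 0.3 = 0.4 to 2.66 × 0.8 = 2.1 outside the definition.

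This covers both arms together. It is an upper bound under those assumptions, because it supposes that no perforation at such a site ever shows intraperitoneal air. It also uses all 266 patients, whereas the adverse event population is restricted to those who underwent the allocated treatment and were followed for up to 28 days.

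**The case against.** The strongest reply is that nothing is really lost. The adverse event list is open, CTCAE grading applies to adverse events generally, and any event that is life-threatening, or that causes rehospitalization or a longer stay, must be reported as serious. A delayed perforation of the kind described would very probably qualify. **This stands.** A reader might infer from 4c that such perforations disappear from the safety data; the article does not support that. What the event loses is its label.

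A reader might also infer a biased comparison of the arms. That is not supported either. The definition is the same in both arms, nothing in the article shows that the gap would fall more heavily on one of them, and no between-arm test of delayed perforation is named. The adverse event rates that are analysed are not stated to be limited to items a to d, so a relabelled event may still count there.

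It can further be said that 4b and 4c differ for good reason. During the procedure the operator is looking at the site; over the next 28 days no routine endoscopy is described, so imaging is the natural means of confirmation. This explains why imaging leads in 4c, and the two items do not contradict each other. It does not explain why a defect that is in fact seen later should not count, or why only air within the peritoneal cavity should.

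Finally, the article condenses a fuller protocol. But 4c is a stated rule, not an omitted detail, and must be judged as stated.

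**Conclusion.** The point holds as a minor defect of definition. As worded, 4c leaves unclassified a delayed perforation that shows only extraperitoneal air, and one seen directly without imaging that shows intraperitoneal air; neither fits 4b or 4d. The effect is confined to the reported delayed-perforation count. The event can remain in the safety data as another adverse event or a serious one, and the primary R0 analysis is unaffected.

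The size cannot be calculated from the article and is likely a very small number of events. The illustrative range above rests wholly on assumed inputs and should not be quoted as a number of missed perforations. With counts this low, however, one case could decide whether the report shows one delayed perforation or none. The extraperitoneal part of the argument rests on general anatomy; the direct-observation part rests on the article's text alone.

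**What to change.** Define delayed perforation as a bowel perforation within 28 days, without intraoperative perforation, established by either:

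- a defect seen directly at endoscopy or surgery; or
- extraluminal air, intraperitoneal or extraperitoneal, on imaging more than 12 h after treatment.

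Use the same description of air in the imaging limb of 4b, keeping its 12 h limit. Make the change by an amendment notified to the Certified Review Board before analysis. Apply it identically to both arms by re-reading existing reports, and also report the count under the current wording of 4c so that the effect of the change is visible.

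The cost is one amendment and a review of a few reports, with no added imaging, procedures or visits. There are two drawbacks. Recruitment began in June 2022, so this changes an endpoint definition mid-trial in an open-label study; reporting both counts answers most of that. And earlier reports may not have recorded extraperitoneal air, so reclassification of past cases may be incomplete, which should be stated with the results.

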### Standard treatment group (ESD group)

ESD is a procedure involving a mucosal incision and submucosal dissection using ESD knives [38]. ESD knives are specified to the following; DualKnife J (KD-655, Olympus Medical Systems Corp, Tokyo, Japan), FlushKnife BT-S (DK2620J, Fujifilm, Tokyo, Japan), HookKnife J (KD-625, Olympus Medical Systems Corp), and Jet B-knife (Zeon Medical Inc, Tokyo, Japan). The endoscope is selected at the discretion of the operator. CO2 insufflation is recommended. This trial does not specify the type and mode of the electrosurgical unit, the use of a distal attachment, or the type of solution for submucosal injection. Traction devices are allowed to use. In cases of intraprocedural bleeding, hemostasis is achieved through coagulation with the tip of the ESD knife or hemostatic forceps. If intraprocedural perforation or muscle injury occurs, the resection site will be clipped.

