### Restrictions after resection

In the absence of perforation or muscle injury, prophylactic clipping or covering methods, such as polyglycolic acid sheets and fibrin glue, are not recommended, however, they are permitted. If the operator applies prophylactic clipping or covering methods, they are required to apply the same method to both the ESD and ESMR-L groups. Prophylactic endoscopic coagulation is permitted only for visible vessels.

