### Statistical analyses

The main analysis will be conducted using the full analysis set (FAS). The FAS is defined as the population of enrolled participants, excluding any of the following criteria: (1) any violation of the inclusion or exclusion criteria, (2) no treatment for the enrolled lesion, (3) no data after randomization, or (4) histologically no NET or NEC after treatment completion. Additionally, a complementary analysis will be conducted using the per-protocol set (PPS), which includes participants from the FAS who have completed the allocated treatment. Adverse events will be assessed in the population of enrolled participants who have undergone the allocated treatment and have been followed up for up to 28 days after the procedure.

The primary assessment parameters, R0 resection rate in each group, and differences between the groups are analyzed. The 90% CI for the difference will be calculated using the Miettinen–Nurminen method. To assess the non-inferiority of ESMR-L, the difference between the groups will be compared to the non-inferiority margin of 8% using a Farrington–Manning test with a one-sided alpha of 0.05. If non-inferiority is demonstrated, the superiority of ESMR-L will be examined using a one-sided alpha of 0.05.

The secondary assessment parameter, en bloc resection rate, will be analyzed using the same method as the primary endpoint. The procedure time, number of hospitalization days, and total cost of the devices and agents are compared using the Wilcoxon rank-sum test. The rates of adverse events between the groups with and without closure of the resection site will be compared using Fisher’s exact test.

A subgroup analysis by expert and non-expert endoscopists will be performed for the primary endpoint, rate of adverse events, and procedure time. Comparison between expert and non-expert endoscopists will be also performed. Factors associated with R0 resection failure will be analyzed using logistic regression.

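### Secondary endpoint 7 mixes therapeutic with prophylactic closure, so its adverse-event comparison is biased against closure and can make a neutral or protective closure look harmful

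*Protocol article*

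**What the plan says.** All of the following is in the protocol article.

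- **Who is closed by rule.** The ESD section states "If intraprocedural perforation or muscle injury occurs, the resection site will be clipped", and the ESMR-L section has the same sentence.
- **Who else may be closed.** Under Restrictions after resection, prophylactic clipping or covering without injury is discouraged but allowed ("are not recommended, however, they are permitted"). An operator who uses such a method must use it in both arms ("If the operator applies prophylactic clipping or covering methods, they are required to apply the same method to both the ESD and ESMR-L groups"). The ESMR-L section also lists clipping among the means of stopping bleeding straight after resection. The ESD section names only knife-tip coagulation and haemostatic forceps for intraprocedural bleeding.
- **How the groups are formed.** Secondary endpoint 7: "Patients who undergo closure of the resection site using clips or detachable snares will be compared with those without closure". The reason for closure plays no part.
- **What counts as an event.** Secondary endpoint 4 lists delayed bleeding, intraoperative perforation, delayed perforation and electrocoagulation syndrome. The second has two routes: "Intraoperative perforation: defect in the muscular layer observed during the procedure, or the presence of free air in the peritoneal cavity". For the free-air route, the scan has to take place no more than 12 h after the procedure.
- **How they are compared.** Statistical analyses: "The rates of adverse events between the groups with and without closure of the resection site will be compared using Fisher’s exact test". The section does not exclude injured patients, limit the events to those after closure, or adjust.

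**The concern.** Closure can only influence what happens after it. A perforation seen during the procedure comes before the clip and is the reason for it. Under endpoint 7 that perforation is nevertheless counted as an adverse event of the closure group, while a patient left unclosed will rarely carry one. This is reverse causation built in by the grouping rule. Because prophylactic closure is discouraged, the closure group may be small, and a few injured patients could then dominate its event rate.

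At stake is the reading of a named secondary endpoint. It could report harm from closure that is an artefact of the grouping, or hide a real reduction in delayed events.

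**Working it through.** **No figure to reproduce.** The article gives no rate, power or sample size for endpoint 7. The only input taken from it is the total of 266 (Sample size calculation). This is an upper limit, since adverse events are assessed only in patients who had the allocated treatment and were followed up. Every rate below is an assumption.

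**Step 1: fixed tables with no true effect.** Let *k* perforations all be recognised and clipped, and let a share *s* of the other 266 − *k* patients be closed prophylactically. Later events occur at 3% whether closed or not. All adverse events are counted together. For *k* = 8 and *s* = 20%: 258 × 0.20 ≈ 52 closed prophylactically, with 52 × 0.03 ≈ 2 later events. The closure group is then (8 + 2)/(8 + 52) = 10/60. The other group has 206 patients and 206 × 0.03 ≈ 6 events.

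| Perforations | Prophylactic closure | Closure | No closure | Fisher p (two-sided) |
|---|---|---|---|---|
| 8 | 20% | 10/60 (16.7%) | 6/206 (2.9%) | 0.0005 |
| 5 | 20% | 7/57 (12.3%) | 6/209 (2.9%) | 0.009 |
| 3 | 20% | 5/56 (8.9%) | 6/210 (2.9%) | 0.057 |
| 8 | 50% | 12/137 (8.8%) | 4/129 (3.1%) | 0.07 |
| 5 | 50% | 9/135 (6.7%) | 4/131 (3.1%) | 0.26 |
| 3 | 50% | 7/135 (5.2%) | 4/131 (3.1%) | 0.54 |

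Two of the six are significant at 5%, but all six point to harm although none exists. Leaving the 8 perforated patients out of the first row gives 2/52 against 6/206, p = 0.66. The apparent effect in that row comes from the grouping.

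**Step 2: when the direction reverses.** Let *q* be the perforation rate, *b* the later event rate without closure, and RR the true relative risk under closure. The expected rates are

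- closure: [q + (1 − q)·s·b·RR] / [q + (1 − q)·s]
- no closure: b

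Closure looks worse in expectation when q(1 − b) > (1 − q)·s·b·(1 − RR).

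- *q* = 2%, *s* = 30%, *b* = 3%, RR = 1: (0.02 + 0.00882)/0.314 = 9.2% against 3.0%.
- The same with RR = 0.5: (0.02 + 0.00441)/0.314 = 7.8% against 3.0%.
- *q* = 0.5%, *s* = 50%, *b* = 6%, RR = 0: 0.005/0.5025 = 1.0% against 6.0%. Here the benefit still shows.

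For *s* from 10% to 50%, *b* of 3% or 6% and RR of 0.5 or 0, the break-even number of perforations among 266 runs from 0.4 to 8.2.

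**Step 3: simulation of the planned Fisher test at N = 266.** In the first case of step 2, a neutral closure is declared significantly harmful in about 50% of trials. In the second, a closure that halves later events points the wrong way in about 94%. In the third, significant benefit appears in about 56%. With perforated patients removed and only later events counted, a neutral closure is declared harmful in about 2%.

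**The case against.** Four points can be made in defence of the plan.

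1. **Pooling is not stated.** The article defines four event types and does not say that they form one composite. The full protocol or analysis plan may test them by type. This stands in part: delayed bleeding, tested alone, would not count perforations as events. Injured patients would still sit in the closure group, however, and a by-type test of intraoperative perforation would be circular.
2. **The rates are assumed.** This stands. Four of the six tables above are not significant, and with no perforations this route adds no bias.
3. **Endpoint 7 is a non-randomised secondary comparison with no hypothesis, margin or power.** This stands, and it limits the severity. It does not excuse a grouping rule that lets the outcome determine the exposure.
4. **The same-method rule.** It limits imbalance between arms in prophylactic closure. It has no bearing on clipping triggered by injury.

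A reader might also object that sites covered only by sheets or glue fall in the no-closure group, or that closure follows operator habit. The first is simply the stated definition (clips or detachable snares). The second applies to any non-randomised comparison, and the article makes no causal claim for endpoint 7. Neither is an error in the plan.

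**Conclusion.** The point holds as a bias against closure. The mandatory clipping rule, the closure definition and the adverse-event list together let a recognised perforation create its own exposure, and nothing in the article corrects for this. A neutral or protective closure can therefore look harmful.

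A reader might infer more: that every intraoperative perforation lands in the closure group, and that closure must look harmful whatever its true effect. The article supports neither. Its definition also admits perforation shown only by free air on imaging within 12 h, and such a site need not have been clipped. With few perforations and a strong benefit, closure can still come out ahead, as the third case in step 2 shows.

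The size is unknown. Under the assumptions of step 1 (266 patients, 3% later events, no true effect, all events pooled, every perforation clipped), p lies between 0.0005 and 0.54. The primary R0 comparison and its non-inferiority conclusion are untouched. Severity is moderate.

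**What to change.** Change the analysis definition of endpoint 7; treatment stays as it is.

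- Restrict the comparison to patients without intraprocedural perforation or muscle injury.
- Show separately, or leave out, patients clipped only for bleeding immediately after resection. The ESMR-L section names this use of clips, so removing injured patients does not by itself leave only prophylactic closure.
- Count only events that arise after closure: delayed bleeding, delayed perforation and electrocoagulation syndrome.
- Label the result non-randomised and exploratory. Stratifying by randomised arm is optional.

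The cost is a slightly smaller analysed set and one data check. Perforation and the delayed events are already recorded as adverse events. Muscle injury is not named in that list, and the article does not say that the reason for clipping is recorded. The sponsor should confirm that the EDC system captures one or the other; if it does not, a field is needed, and the change is then more than wording.
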